##### **Safety population**

All randomized mothers and EPT infants will be evaluable for adverse events from the time of delivery.

##### **Per Protocol population**

A per protocol population will be used for secondary sensitivity analyses of the primary and secondary outcomes and will include all randomized EPT infants that do not have protocol deviations: 1) Eligibility violation 2) Intervention non-adherence 3) Intervention crossover 4) Missing primary outcome information.

### **Analyses of the Primary Endpoint**

The primary outcome of the trial is based upon the central review and is the proportion of EPT infants who are alive without any grade IVH on head ultrasound obtained 7-10 days following birth. (Section 6.1.1) EPTs infants will be followed until 36 weeks PMA or discharge home or death, whichever comes first. The primary outcome will be assessed within each cohort separately. The primary outcome classification is binary and the stratified Cochran-Mantel-Haenszel test for relative risk will be used for the comparison of intervention arms stratified by gestation age (GA) at randomization. A 95% confidence interval for the relative risk within cohort will be constructed. Although the randomization unit is the mother, the analysis unit is the infant. Initial analyses will assume independence for twin outcomes. Subsequent analyses may employ a permutation test to confirm the results under the assumption of independence.

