#### **Twins**

**Centers may consider enrolling twins once they have completed the VentFirst intervention on at least 3 singleton C-section Vent First deliveries**, in order to gain experience with setting up and carrying out the VentFirst protocol. At that point, the site PI and site Obstetrician can opt to begin approaching **mothers of twins (dichorionic only)** about participation in the study. Team training on logistics of twin VentFirst deliveries should be carried out prior to randomizing any twin gestations. The site PI or site Obstetrician may opt to not enroll twins.

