### **Randomization**

Study eligibility and consent must be confirmed prior to randomization.

Randomization should be done as close to the expected time of delivery as possible, preferably within one hour. At each site, randomization will be done by the Clinical Research Coordinator (CRC) or a trained member of the study team via a web-based platform.

The CRC or trained team member will login to the randomization module, enter the current estimated gestational age, and request a study arm assignment. The server will provide the arm assignment based on a randomization scheme specified by the project biostatistician along with a single use alphanumeric transaction identifier consisting of a color and a 2-digit number, such as "red51." The server will display the transaction identifier, site code, transaction time, gestational age and arm assignment to the requesting personnel.

A delivery room script specific to the study arm "Standard 30-60 second" or "VentFirst-120 second" will be available to the neonatology team attending the delivery. The transaction identifier must be recorded on the appropriate delivery script.

**Twins will automatically be assigned to the same study intervention and will have the same transaction identifier but will be assigned a unique subject number in the MuSIC database.**

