### Randomization and stratification

For this study, the randomization unit is the mother and the analysis unit is the EPT infant. Thus, twins are assigned the same intervention. Within

each site, mothers will be stratified by expectant infant GA categories without regard to cohort. Initial randomization will occur with equal allocation to each arm using a stratified block randomization scheme with varying block sizes (of size 2-6). Although we cannot determine cohort designation (breathing well or not) at randomization, given the large target sample size we assume that the randomization process will result in approximate balance between arms within cohort. However, if a significant imbalance is noted in cohort 1 as assessed by the DSMC then a weighted minimization scheme will be used to maintain arm balance within cohort 1. If balance is maintained, infants will continue to be randomized with equal allocation to each arm using the stratified block randomization scheme. Given that a 40/60% or a 30/70% arm imbalance reduces power to 78% or 73%, respectively, the randomization scheme will be modified if a 30/70% arm imbalance is observed in cohort 1, or as deemed appropriate by the DSMC. Note, the probability of a 30/70 split or more extreme in either arm in cohort 1 is  $<0.001$ .

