### **Study Size Considerations**

It is hypothesized that the investigational approach (VentFirst) improves outcomes in both cohorts with a greater effect in cohort 1 (not breathing

well), thus, the assumption of a common effect is violated and the two cohorts will be assessed separately. However, target sample size is based upon attaining a sufficient number of accruals to both cohorts. Based on discussions with investigators who have recently conducted delayed cord clamping trials in preterm infants, in addition to experience in our own Pilot Trial, it is anticipated that ~50-65% of EPTs infants will be categorized as ‘breathing well.’

The Cochrane meta-analysis of the effect of timing of umbilical cord clamping in preterm infants (delayed 30 or more seconds versus immediate) reported an estimated odds ratio (95% CI) of 0.59 (0.41-0.85) for survival without IVH. The Cochrane analysis included some infants up to 37 weeks gestational age where the differences in outcome affected by DCC may not be as large as might be expected in a cohort restricted to more immature infants. Furthermore, by restricting Cohort 1 to EPT infants who are not breathing well, it is hypothesized that the outcome effect will be even greater. Therefore, for this study we expect to see a larger reduction in our primary endpoint in the EPT infants in cohort 1 (odds ratio of 0.5) and a reduction on the order of magnitude observed in the Cochrane analysis or slightly more (odds ratio of 0.59 or 0.55) in the EPT infants in cohort 2.

Within each site, infants will be stratified by gestational age (GA 230/7 to 256/7 weeks; GA 260/7 to 286/7 weeks). Numbers of inborn infants 24-28 weeks’ GA without major birth defects at Vermont Oxford Network (VON) centers in the United States (670 centers) born in 2013 were used as the baseline estimates of the primary event rate. The information is summarized in the following table.

| Strata:
GA week/day                 | Proportion of newborns
in each strata | “Success”
% Alive without
IVH at day 7-10 | “Failure”
1-%Success |
|----------------------------------------|------------------------------------------|-------------------------------------------------|-------------------------|
| 23 0/7 to 25 6/7 | 0.38                                     | 44.9%                                           | 55.1%                   |

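### The primary test and its confidence interval treat twins as independent although twins are randomized together; the resulting error is probably small, but it is anti-conservative and cheap to remove

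*Protocol*

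**What the plan says.** Protocol section 7, Randomization and stratification, states that "the randomization unit is the mother and the analysis unit is the EPT infant. Thus, twins are assigned the same intervention". Section 4, Randomization, confirms it: "Twins will automatically be assigned to the same study intervention".

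Section 7, Analyses of the Primary Endpoint, specifies a CMH test stratified by GA, within each breathing cohort, with a 95% confidence interval for the relative risk. On twins it says "Initial analyses will assume independence for twin outcomes", followed by "Subsequent analyses may employ a permutation test to confirm the results under the assumption of independence". Nothing says which result governs if the two differ, or whether the permutation is of mothers or of infants.

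Study Size Considerations counts infants: 172 per arm in cohort 1 (not breathing well) and 298 per arm in cohort 2 (breathing well). It mentions no twin share, ICC or design effect.

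Section 3, Twins, limits twin enrolment to dichorionic pairs. A site may start only after experience with singletons ("Centers may consider enrolling twins once they have completed the VentFirst intervention on at least 3 singleton C-section Vent First deliveries"), and may decline altogether: "The site PI or site Obstetrician may opt to not enroll twins".

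**The concern.** A twin pair is a cluster of two, allocated as a unit. When both members are in the same arm, a positive within-pair correlation adds to the variance of the arm comparison. A CMH variance computed as if infants were independent leaves that term out.

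The two GA strata each span three weeks. They remove part of what twins share but not all of it: exact gestation within the stratum, the delivery, maternal treatment and site remain common to the pair. A positive residual correlation is therefore the natural expectation, although the protocol does not state one.

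The error favours a false positive on the primary test of a Phase III trial. Section 2.2 ties resuscitation guidance to whether each hypothesis is supported, so a p-value just inside the boundary could settle a recommendation because of the independence assumption alone. The optional permutation test does not prevent this: it need not be done, and permuting infants instead of mothers would repeat the same assumption.

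**Working it through.** **1. Reproduce the stated power.** Inputs from Study Size Considerations: GA strata with shares 0.38 and 0.62, control failure rates 55.1% and 25.6%, odds ratio 0.5 applied in each stratum, 172 infants per arm, uncorrected CMH, two-sided 5%. The odds ratio gives VentFirst failure rates of 38.0% and 14.7%. With independent infants the power is **79.9%**, against the stated 80%. The other cohort 1 cells at this size give 68.3% and 58.0% (stated 68% and 58%). Cohort 2 with 298 per arm and odds ratio 0.59 gives 81.4% (stated 81%). The protocol's figures are thus independence figures, with no allowance for twins.

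**2. Share of cohort 1 infants that matters.** Cohorts are defined by each infant's own breathing and analysed separately, so only pairs with both twins in the same cohort inflate the variance. Let t be the proportion of infants who are twins and r the correlation of breathing status within a pair (both assumed). With the protocol's 37% cohort 1 share:

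f = t × [0.37 + r × 0.63]

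With r = 0.3 the bracket is 0.37 + 0.189 = 0.559. So t = 10% gives f = 5.6%, and t = 20% gives f = 11.2%.

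**3. Design effect and consequences.** D = 1 + f × ICC, where ICC is the outcome correlation within pair and GA stratum.
- Actual two-sided type I error of the nominal 5% test = 2Φ(−1.96/√D)
- Power of a correctly clustered test = Φ(2.80/√D − 1.96), where 2.80 = 1.96 + 0.84 corresponds to 80% power

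| Twins t | f | ICC | D | Type I error | Power |
|---|---|---|---|---|---|
| 10% | 0.056 | 0.1 | 1.006 | 5.1% | 79.8% |
| 10% | 0.056 | 0.3 | 1.017 | 5.2% | 79.3% |
| 10% | 0.056 | 0.6 | 1.034 | 5.4% | 78.7% |
| 20% | 0.112 | 0.1 | 1.011 | 5.1% | 79.6% |
| 20% | 0.112 | 0.3 | 1.034 | 5.4% | 78.7% |
| 20% | 0.112 | 0.6 | 1.067 | 5.8% | 77.4% |

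In the last row the true standard error is √1.067 = 1.033 times the naive one, and keeping 80% power would take 172 × 1.067 ≈ 184 infants per arm.

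**4. Upper end.** f = 0.30 with ICC 0.6 gives D = 1.18, type I error 7.1% and power 73.2%. To reach f = 0.30 in cohort 1, the proportion of all infants who are twins would have to be 0.30/0.37 = 81% if breathing is independent within pairs, 0.30/0.559 = 54% at r = 0.3, and 0.30/0.685 = 44% at r = 0.5. Only with perfect concordance would 30% twins suffice.

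**5. Check of the formula.** Simulation of the GA-stratified CMH test (344 infants, 20,000 trials per setting) gave a naive type I error of 5.7% at f = 0.20, ICC 0.3 (formula 5.7%) and 6.7% at f = 0.30, ICC 0.5 (formula 6.8%). With the variance computed by mother, the same trials gave 5.1% and 4.9%.

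**6. Interim look.** The cohort 1 efficacy bound is |Z| > 2.611, nominal p = 0.009. Over the rows in step 3, 2Φ(−2.611/√D) runs from 0.009 to 0.012.

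**The case against.** The strongest reply is that the effect is small and partly acknowledged. The protocol discloses the mismatch of units, calls the independence analysis an initial one and names a follow-up test. Twins are dichorionic only, sites may decline them, and pairs that differ in breathing fall into different cohorts. Conditioning on GA stratum absorbs some of the correlation. A loss of one or two points of power is within the wording of approximately 80%.

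Almost all of this stands as to size, and it is why the moderate range above is the one to quote. It does not answer the point itself. Using independence for the primary result is a choice the protocol states, not a detail left to the statistical analysis plan. The follow-up test is optional, does not name its unit and has no stated standing against the primary result.

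It is also fair to object that the type I errors are for a single look at 1.96, whereas cohort 1 has two looks with bounds 2.611 and 1.987. The figures therefore illustrate the inflation and are not the error rate of the two-look procedure.

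**Conclusion.** The point holds in direction, with a modest and uncertain size. Under any positive within-pair correlation inside GA strata, the planned p-values and intervals are anti-conservative and the power is somewhat optimistic. For cohort 1, with 10-20% twins, breathing correlation 0.3 and ICC 0.1-0.6 (all assumed), the type I error is about 5.1-5.8% and power about 77-80%.

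The documents do not support three stronger readings:
- A reader might infer that the 80% was miscalculated. It was not: it reproduces under the independence it assumes.
- A reader might infer that the type I error is about 7% and power about 73%. Those values need 30% of cohort 1 infants to have a co-twin in the same cohort and an ICC of 0.6, which step 4 shows to be a demanding combination.
- A reader might infer that leaving site out of the CMH strata makes the false-positive problem worse. Omitting a stratification factor generally makes a test conservative, and in simulation adding 12 sites moved power by only about −1 to +2 points. It is no part of this concern.

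**What to change.** Make the mother the unit of inference for the primary test and its 95% interval in both cohorts. Either of these would do:
- a GA-stratified relative risk from a log-link (modified Poisson) generalized estimating equation, with robust variance clustered on mother; or
- a mandatory permutation test that permutes arms between mothers within randomization strata, with an interval that is also clustered on mother.

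Use the same statistic at the cohort 1 interim look. Keep the independence CMH as a sensitivity analysis, and state that the mother-level result governs. In Study Size Considerations, state an assumed twin share, same-cohort concordance and ICC, and give the resulting power for each cohort.

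This is a change of wording and needs no new data beyond the mother identifier. The cost is a slightly wider interval and a slightly lower stated power (up to about 3 points for cohort 1 in the moderate range). If few twins are enrolled, the results will barely change.

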### **Analyses of the Secondary and Tertiary Endpoints**

Adverse events will be tabulated by frequency and severity, overall and by arm as well as by cohort. Differences in the level of adverse events by study intervention will be assessed by classifying them as severe or not severe and examining the relative proportion of severe events.

Secondary endpoints for mothers and EPT infants are listed in Section 6.1.2. All endpoints will be summarized with descriptive measures by arm within cohort and overall. For all measures, initial analyses will be performed within cohort. In general, regression analysis consistent with the scale of the outcome measure will be used; logistic regression for binary outcomes; linear regression for continuous outcomes; Poisson or negative binomial for count outcomes all with independent variables for stratification factor and intervention assignment. 95% confidence intervals around the estimates will be constructed. The product-limit method of Kaplan-Meier will be used to estimate time to event type distributions such as survival to 36 weeks PMA and a stratified log rank test will be used to assess differences in survival by arm.

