### **Primary Adverse Event Outcome Measures**

#### ***Maternal***

- 1) Post-partum hemorrhage in the first 24 hours after delivery (≥1000 ml estimated blood loss) (y/n)
- 2) Maternal RBC transfusion (y/n)
- 3) Post-partum delivery-related infection prior to hospital discharge (y/n)
- 4) Retained placenta (y/n)

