### **Demographic and Baseline Characteristics**

Demographic and baseline characteristics will be summarized for all eligible mothers and EPT infants registered to the study by cohort and intervention arm.

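### The within-cohort analysis rule does not fit maternal outcomes: a mother has no breathing cohort of her own, and the modelled maternal comparison is split when all randomised mothers could be compared by arm

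*Protocol*

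**What the plan says.** Under Analyses of the Secondary and Tertiary Endpoints (protocol Section 7), the protocol introduces the endpoints with "Secondary endpoints for mothers and EPT infants are listed in Section 6.1.2". It promises that "All endpoints will be summarized with descriptive measures by arm within cohort and overall", and then sets the rule "For all measures, initial analyses will be performed within cohort". The regression models and 95% confidence intervals follow from that rule. For adverse events the same section says "Adverse events will be tabulated by frequency and severity, overall and by arm as well as by cohort"; the Synopsis repeats this.

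Under Randomization and stratification the unit is fixed: "For this study, the randomization unit is the mother and the analysis unit is the EPT infant". No exception is made there for maternal outcomes.

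The Study Design table in Section 7 defines the cohorts by how the infant breathes 20-30 seconds after delivery. Section 3 (Twins) allows dichorionic twins at the site's option, and Section 4 gives both twins the same arm.

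Section 6 lists six primary adverse event outcomes. Four are maternal: "Post-partum hemorrhage in the first 24 hours after delivery", red cell transfusion, delivery-related infection and retained placenta.

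**The concern.** Whether clamping at 120 seconds harms mothers is a question about the randomised unit, the mother, across the whole trial. Cohort belongs to the infant. A singleton mother can borrow her infant's label, but a mother of one infant breathing well and one not breathing well has two labels, and the protocol gives no rule for her.

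Two things are at stake. The first is precision: analysing maternal outcomes within cohort divides the mothers into two smaller comparisons, and no modelled comparison of all mothers is specified. The second is the counting unit. If the infant unit were carried over literally, a mother of twins would contribute her outcome twice in one cohort or once in each. Duplicated records would then be treated as independent.

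**Working it through.** **The plan's own figure.** The protocol states no power or rate for any maternal outcome. Its nearest figure is for the infant primary endpoint: 172 per arm in cohort 1, odds ratio 0.5, about 80% power. I used a two-stratum uncorrected Cochran-Mantel-Haenszel normal approximation with strata 0.38/0.62, failure rates 55.1%/25.6% and two-sided 5%. It gives 79.95%, so the figure reproduces. It confirms the cohort sizes but does not bear on mothers.

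**Inputs from the protocol.** 940 infants; 172 and 298 infants per arm in cohorts 1 and 2; cohort shares 0.37 and 0.63.

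**Inputs assumed.** Twin share of infants t = 20% (range 10-30%); control hemorrhage rate 10% (range 5-20%).

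**Number of mothers.** 940(1 − t) + 940t/2 = 893, 846 and 799 for t = 10%, 20% and 30%. At 20% this is 423 per arm, with 940 × 0.20/2 = 94 twin mothers.

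**Mothers with a twin in each cohort.** If twins' breathing were independent, 94 × 2 × 0.37 × 0.63 ≈ 44. Positive correlation within pairs would lower this.

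**Precision.** Power = Φ[(|p₁ − p₂| − 1.96·SE₀)/SE₁], with SE₀ = √(2p̄(1 − p̄)/n) and SE₁ = √((p₁(1 − p₁) + p₂(1 − p₂))/n).

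Example, cohort 1, 10% against 15%: p̄ = 0.125, SE₀ = 0.0357, SE₁ = 0.0356, so Φ[(0.05 − 0.0699)/0.0356] = Φ(−0.56) = 29%.

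Power for a relative risk of 1.5:

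| Control rate | Cohort 1 (172/arm) | Cohort 2 (298/arm) | All mothers (423/arm) |
|---|---|---|---|
| 5% | 16% | 24% | 32% |
| 10% | 29% | 45% | 59% |
| 15% | 43% | 65% | 80% |
| 20% | 57% | 81% | 92% |

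Solving the same formula for 80% power at a 10% control rate gives a detectable increase of 10.9 points in cohort 1, 7.9 in cohort 2 and 6.5 pooled (6.3-6.7 for 10-30% twin infants). The cohort columns use infants as if each had a different mother, so they are slightly favourable to the within-cohort analysis.

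**If twin mothers were counted per infant.** With equal risk in singleton and twin mothers, duplicating each twin mother's record inflates the variance by (1 − t) + (t/2) × 4 = 1 + t. The true level of a nominal 5% test is 2[1 − Φ(1.96/√(1 + t))]:

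- t = 10%: 6.2%
- t = 20%: 7.4%
- t = 30%: 8.6%

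That is for a pooled test. Within a cohort only concordant pairs are duplicated. At t = 20% with independent breathing status the inflation is 1 + 0.20 × 0.37 = 1.074 in cohort 1 and 1 + 0.20 × 0.63 = 1.126 in cohort 2, which gives about 5.9% and 6.5%.

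**The case against.** Three stronger readings are tempting, and the protocol does not support them.

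*That the protocol plans to count twin mothers twice.* A reader might infer this from the infant unit, but it is not stated for maternal outcomes. The unit sentence sits in the randomisation text, where it leads to twins sharing an arm; the similar sentence under Analyses of the Primary Endpoint concerns the infant endpoint. Section 4 describes hemorrhage as an event of the mother, Section 8 lists maternal and infant events in separate blocks, and the Safety population names mothers in their own right. Double counting is left open, not announced.

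*That the maternal comparison is only ever split in two.* Endpoints are also summarised overall, adverse events are tabulated overall and by arm, and only the initial analyses are tied to cohort. Hemorrhage is classed as an adverse event outcome and does not appear in the list headed Secondary, which is neonatal. The adverse event sentence may therefore govern it. This stands in part: the protocol does not settle which sentence applies. But the overall endpoint summary is descriptive, and the stated adverse event comparison looks at the proportion of events that are severe, not at risk per mother.

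*That cohort is irrelevant to mothers.* It is not. In the Standard arm clamping may be at 30-60 seconds if the infant is not breathing well and is at 60 seconds otherwise. The added delay to 120 seconds is thus 60-90 seconds in cohort 1 and 60 in cohort 2. The guideline statements in Section 2.2 also depend on cohort. Within-cohort maternal tables therefore inform a stated decision, and a baseline summary of mothers by cohort suits a primary comparison made within cohort.

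It can also be said that one record per mother is a dataset rule for the statistical analysis plan, which is not at hand and may settle it. That is fair for the record rule alone. It does not answer the within-cohort rule, which the protocol itself states for all measures.

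**Conclusion.** The point holds as a mismatch between a blanket rule and the outcomes it covers. The protocol names maternal endpoints, sends all measures to a within-cohort initial analysis, and defines neither a mother's cohort when her twins differ nor a maternal unit of analysis. The main cost is precision: at an assumed 10% control rate and 20% twin infants, the detectable increase is 10.9 and 7.9 points within cohorts against 6.5 pooled. This loss follows from the within-cohort rule and needs no assumption about double counting. The 6-9% error level is conditional: it applies only if twin mothers' records were duplicated in a pooled test, which the protocol does not plan. All these sizes rest on assumed hemorrhage rates and twin shares. The primary infant analysis is unaffected. This is a worthwhile, low-cost improvement to the maternal safety comparison.

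**What to change.** In Analyses of the Secondary and Tertiary Endpoints, and in the matching Synopsis text on statistical methods, state that:

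- maternal outcomes and maternal adverse events are counted once per mother;
- the main maternal comparison is by randomised arm across all randomised mothers, stratified by GA band at randomisation, with an estimate and 95% confidence interval;
- within-cohort maternal tables are kept as supportive output, with a stated rule for mothers whose twins fall in different cohorts;
- the within-cohort rule for initial analyses applies to infant measures.

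The baseline summary by cohort and arm needs no change. The cost is wording and one extra pooled analysis, with no new data. The only loss is that the within-cohort maternal results become supportive.
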